### Eligibility criteria

2.2

The inclusion criteria are as follows: (1) aged 18–75; (2) histologically proven gastric adenocarcinoma on biopsy (papillary adenocarcinoma, tubular adenocarcinoma, mucous adenocarcinoma, signet-ring cell carcinoma or poorly differentiated adenocarcinoma); (3) proven clinical stage of cT1-4a N0/+ M0 by ultrasound endoscopy, enhanced CT/MRI examination or diagnostic laparoscopy according to the TNM classification of the American Joint Committee on Cancer (AJCC cancer staging manual, eighth edition); (4) without distant metastasis and no invasion of adjacent organs; (5) a preoperative Eastern Cooperative Oncology Group (ECOG) score of 0 or 1; (6) a preoperative American Society of Anesthesiologists (ASA) score of I-III; and (7) signed a written informed consent form.

The exclusion criteria are as follows: (1) pregnant or lactating women; (2) patients with severe mental disorder; (3) a history of upper abdominal surgery (with exception of laparoscopic cholecystectomy); (4) a history of gastrectomies, endoscopic mucosal resection (EMR) or endoscopic submucosal dissection (ESD); (5) enlarged or bulky regional LNs according to preoperative imaging and larger than 3 cm at the long diameter; (6) the tumor invades the duodenum or esophagus; (7) Borrmann type IV GC; (8) history of other malignant tumors within the last 5 years; (9) received previous neoadjuvant radiotherapy or chemotherapy; (10) history of myocardial infarction or unstable angina within the last 6 months; (11) history of cerebrovascular accident within the last 6 months; (12) undergoing sustained systemic corticosteroid treatment within 1 month prior to surgery; (13) emergency surgery due to GC complications (bleeding, perforation, or obstruction); and (14) FEV1 <50% predicted value.

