### Randomization and blinding

2.3

The patients were enrolled by a dedicated surgeon on our team. For eligible patients treated with GC at The Fourth Hospital of Hebei Medical University, thoracoabdominal CT, echocardiography, ultrasound of supraclavicular LNs, sonography of lower extremity veins, electrocardiogram and lung function examination should be performed before the operation. The patients who meet the inclusion criteria and are feasible for radical onco-surgery are then randomized to receive either endoscopic injection of CNSI (CNSI group) or endoscopic injection of ICG (ICG group) during gastroscopy at a 1:1 ratio. Randomization has been achieved using a random number table by the data manager, and the allocation is not concealed. While the blinding of the surgeons or participants is impossible, the pathologists are blinded to the types of surgical approaches.

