### Outcomes

2.5

The primary outcome of this study is to determine the number of LNs retrieved. The secondary outcomes are to determine the LN staining (or fluorescence) rate (Number of staining or fluorescence LNs/Total number of retrieved LNs), LN staining (or fluorescence) rate at each station, stained (or fluorescent) LN positive rate(Number of staining or fluorescence positive LNs/Total number of positive LNs), stained (or fluorescent) LN negative rate(Number of staining or fluorescence negative LNs/Total number of negative LNs), nonstained (or nonfluorescent) LN positive rate(Number of nonstaining or nonfluorescence positive LNs/Total number of positive LNs), nonstained (or nonfluorescent) LN negative rate(Number of nonstaining or nonfluorescence negative LNs/Total number of negative LNs), LN metastasis rate(Number of metastasis LNs/Total number of retrieved LNs), number of metastatic LNs, complication and mortality rates within 30 days, 3-year disease-free survival (DFS), 3-year overall survival (OS), recurrence pattern within 3 years, intraoperative blood loss volume, time spent retrieving LNs, and postoperative recovery (exhaust time after surgery, feeding time after surgery, duration of postoperative hospital stay).

Any complications should be recorded and reported. There are mainly two complications related to the procedure: intraoperative complications and postoperative complications. The former includes bleeding, injuring the viscera, lymphatic leakage and so on. The latter should be classified according to the Clavien−Dindo classification system.

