### Data collection and analysis

2.8

Designated and trained surgeons collect the data from the pathology reports and operative reports. The focus of the data should contain clear information about the tumor location, tumor size, histopathologic type, tumor differentiation degree, Lauren classification, vascular tumor embolus, nerve invasion, immunohistochemistry results and pathological findings of the LNs at each station. Long-term prognosis data are collected *via* follow-up up until 3 years after the surgical operations. The follow-up should consist of a 3-month interval from 0–2 years and a 6-month interval in the third year. The main follow-up items included routine physical examination, tumor marker detection (CEA, CA199, CA724 and AFP), abdominal CT, and annual electronic gastroscopy. The follow-up included an outpatient follow-up, a telephone follow-up and a short message platform follow-up. Further evaluation and treatment should be performed if relapse occurs.

The purpose of this study is to compare the safety and efficacy of CNSI and ICG during radical gastrectomy. The primary objective is to determine the number of LNs retrieved. Comparability analysis will be performed on the baseline data to determine whether the two groups are comparable. The number of patients, mean, standard deviation, median, maximum, and minimum will be listed. Descriptive data will be presented as the mean ± SD, while categorical data will be presented as the number and percentage (%). The independent samples t test or nonparametric test will be used to analyze continuous data, and the chi-square test or Fisher’s exact test will be used to analyze categorical variables. It is valuable to analyze the influence of CNSI (ICG) staining or other factors on the number of LNs detected according to the statistical analysis. We can also research the effect of CNSI (ICG) staining on the operative time, intraoperative bleeding volume, intraoperative transfusion volume and postoperative complications. Survival analysis will be performed using the Kaplan−Meier method, and the log rank test will be used to test the difference in survival rates between the two groups. SPSS 26.0 statistical software will be used for statistical analysis. P<0.05 will be considered to indicate statistically significant differences.

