## Discussion

3

Despite the serious burden of GC in China, the public awareness of risk factors or warning symptoms and screening is low, and there is a lack of screening programs (20). Therefore, the majority of GC are detected at an advanced stage, and at this moment, LN metastasis usually occurs. It is well known that LN metastasis is one of the most important prognostic factors for GC patients, and D2 LN dissection has gradually become the mainstream treatment to improve patient outcome (21). The mean number of LNs dissected in Western European countries was 29.5, which is slightly higher than that in China (22). This condition might be associated with the insufficient LN dissection intraoperatively and the false idea that postoperative LN dissection should be completed by a pathologist. Currently, an increasing number of studies have begun to focus on LN tracers, and an increasing number of gastrointestinal surgeons have started using carbon nanoparticle suspension injection or indocyanine green.

A number of interesting differences were identified through our analyses of CNSI and ICG. First, taking an appropriate amount of time to dissect LNs as an example, the LNs are stained black using CNSI, while the LNs labeled with ICG have the ability to generate strong fluorescence emission in certain cases. When utilizing CNSI as a tracer of LNs, surgeons can dissect the LNs under direct vision without the assistance of other instruments. However, if surgeons intend to use indocyanine fluorescence imaging to guide the postoperative nodal dissection, the fluorescence imaging mode must be available, and the wear and tear of the instrument and the burden on surgeons and operating room nurses will increase, which may prolong the time needed for dissecting the LNs. Second, compared with CNSI, ICG may have the potential to decrease the risk of anastomotic fistula with the assistance of examining the blood supply of the anastomosis. Third, CNSI extravasation into gastric serosa will contaminate the surgical fields and increase the difficulty of surgically dissecting the gastric tumor, but surgeons can switch between the fluorescence mode and normal mode to avoid the adverse effects caused by ICG extravasation (15).

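### DFS and OS are compared with a plain log-rank test although clinical stage, assessed before randomization and spanning cT1-4a N0/N+, could be used; the test is valid but costs a little power and is misleading when the arms differ by chance in stage

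*Protocol article*

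**What the plan says.** Section 2.5 (Outcomes) lists among the secondary outcomes "3-year disease-free survival (DFS), 3-year overall survival (OS), recurrence pattern within 3 years". Section 2.8 (Data collection and analysis) gives the method: Kaplan-Meier estimation, and "the log rank test will be used to test the difference in survival rates between the two groups". It names no strata, covariates or Cox model for survival. The remark in 2.8 about other factors concerns the number of lymph nodes detected, not survival.

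Section 2.2 (Eligibility criteria) requires "proven clinical stage of cT1-4a N0/+ M0 by ultrasound endoscopy, enhanced CT/MRI examination or diagnostic laparoscopy". Section 2.3 (Randomization and blinding) puts assignment after eligibility: "The patients who meet the inclusion criteria and are feasible for radical onco-surgery are then randomized". It adds: "Randomization has been achieved using a random number table by the data manager, and the allocation is not concealed". No stratification by stage is described. Section 2.7 (Sample size) sets 96 patients, 48 per arm. Section 2.8 also plans a baseline comparability check but ties no adjustment to its result. The Discussion states that "LN metastasis is one of the most important prognostic factors for GC patients".

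**The concern.** The entry range mixes patients with very different outlooks, and the variable that separates them is assessed before assignment. With 48 patients per arm and no stratified randomization described, the arms can differ noticeably in stage by chance. A plain log-rank test takes no account of that, so part of a stage difference can be read as a tracer difference. Even when the arms are balanced, a test that ignores a strong prognostic factor uses the same data less efficiently.

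It also matters which variable is chosen. If the comparability check shows an imbalance and adjustment is decided afterwards, the tumor data listed in 2.8 are mostly pathology findings, including nodal findings by station. Those are unsafe covariates here. The trial asks whether the tracer changes how many nodes are retrieved, so pathological N stage may itself depend on the arm. Clinical stage at entry cannot.

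**Working it through.** **The plan's own figure.** The article gives no event number, hazard ratio or power for DFS or OS. Its only calculation, 96 patients, is for node count. The difference is 56.93 - 50.52 = 6.41. No SD is given. Reading the stated β of 0.80 as 80% power, an assumed SD of 10.6 gives n = 2 × (1.96 + 0.84)² × 10.6² / 6.41² ≈ 43 per arm, and 43/0.9 = 47.8, so 48. This says nothing about survival, but it fixes the number of patients available.

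**How often a stage gap arises.** Let p be the share of patients in the worst-stage group. The SD of the difference in that share between arms is sqrt(2p(1-p)/48). With p = 0.6 this is sqrt(2 × 0.6 × 0.4/48) = 0.10, or 10 points. A gap above 15 points means at least 8 of 48 patients (16.7 points). With a continuity correction, 7.5/48 = 15.6 points, or 1.56 SD, which gives a two-sided probability of about 12%. Exact binomial figures for p from 0.5 to 0.7 are about 9-13%. Counting gaps of 7 of 48 (14.6 points) as well raises this to 15-18%.

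**What a 15-point gap does.** Assume 3-year DFS of 92% in the better group and 60% in the worse, with no tracer effect. The cumulative hazards are -ln 0.92 = 0.083 and -ln 0.60 = 0.511. With 67.5% worse-stage patients in one arm and 52.5% in the other:
- mean cumulative hazards: 0.675 × 0.511 + 0.325 × 0.083 = 0.372, and 0.525 × 0.511 + 0.475 × 0.083 = 0.308
- spurious hazard ratio: 0.372/0.308 ≈ 1.21
- spurious 3-year DFS difference: 0.15 × (92 - 60) = 4.8 points

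**Plain against stratified test.** The simulation used 12,000 trials per scenario, 48 per arm, exponential survival within stage, 3-year censoring and no dropout. Stage mixes and 3-year survival are assumed.

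| Scenario (stage mix; 3-year survival) | Events, no effect | Type I error, plain / stratified | Trials with gap ≥15 points in worst-stage share | False positives in those, plain / stratified | Power at HR 0.5, plain / stratified |
|---|---|---|---|---|---|
| 25/35/40%; 95/75/45% | 30.7 | 5.2 / 5.1% | 11.5% | 10.2 / 4.2% | 33.7 / 38.4% |
| 40/60%; 90/50% | 32.6 | 5.1 / 5.0% | 12.2% | 11.7 / 4.9% | 36.0 / 40.5% |
| 50/50%; 90/60% | 24.0 | 4.8 / 5.0% | 13.2% | 8.4 / 5.2% | 27.6 / 30.3% |
| 20/20/30/30%; 95/85/60/35% | 34.0 | 5.2 / 5.7% | 9.7% | 11.1 / 4.9% | 35.9 / 42.5% |

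The power gain at HR 0.5 is about 3-7 points. At HR 0.6 it is about 2-4 points (18-23% plain, 20-27% stratified). When the worst-stage shares differ by less than 5 points (39-42% of trials), the plain test rejects in only 3.4-3.8%. That is how its overall rate stays near 5%.

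**The fix as proposed.** A separate simulation with four cT-by-cN strata, 48 per arm and assumed stage mix and survival gave about 26-28 events under no effect. Power gains were about 2-5 points at HR 0.5 and 3-7 points at HR 0.4. In the 11-12% of null trials with a gap of 8 or more cT3-4a patients, false positives were 9-11% plain and 4-6% stratified. Four strata are therefore workable at this size.

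**Context.** By Schoenfeld's formula, 80% power at HR 0.5 needs 4 × (1.96 + 0.84)² / (ln 0.5)² ≈ 66 events, about twice the 24-34 expected in the table.

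**The case against.** **The full plan is not shown.** A condensed article may leave covariates to the analysis plan, and 2.8 does not exclude adjustment. This stands as a caution. But the article does name a specific test, and the point is that a better one is available, not that detail is missing.

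**The planned test is valid.** This stands in full. A reader might infer that the plain log-rank test has an inflated error rate; it does not, at 4.8-5.2% overall. The excess applies only to trials in which an imbalance has occurred.

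**Unconcealed allocation could make it worse.** A reader might also infer systematic stage imbalance from the lack of concealment. The article states the lack of concealment but gives no ground for any particular shift in stage, so none is counted here.

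**The gain is small and rests on assumptions.** This stands. How strongly clinical stage separates survival in these patients is unknown: the Discussion's prognostic statement concerns nodal metastasis, not imaging-based cN, and the exclusions narrow the range. One run with an assumed milder contrast (3-year DFS of 93/85/75/50%) showed hardly any excess in imbalanced trials (5.3% v 4.2%, within simulation noise).

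**Entry cN may not be recorded.** Either nodal status qualifies, so eligibility does not turn on it, and the data list in 2.8 names neither cT nor cN. This stands as a practical condition on the fix.

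**The plan offers more than a P value.** It does: Kaplan-Meier curves give 3-year estimates per arm. What is not named is a single measure of the difference with its uncertainty.

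**Conclusion.** The point holds as a matter of efficiency and of protection against chance imbalance, not of validity. Stratifying by entry clinical stage would gain about 2-7 points of power at HR 0.4-0.5. In the roughly 10-13% of trials with a gap of more than 15 points in the worse-stage share, it would bring the false-positive rate from about 8-12% down to about 4-6%. Every one of these figures depends on assumed stage mixes and stage-specific survival. It would be wrong to conclude that stratification rescues the survival comparison: DFS and OS are secondary, and power at HR 0.5 stays at roughly 30-43% even when stratified. Severity is minor to moderate.

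**What to change.** In section 2.8, make the DFS and OS comparison a log-rank test stratified by entry clinical stage in broad groups: cT1-2 v cT3-4a, and cN0 v cN+ where it is recorded at entry. Beside the Kaplan-Meier curves, report the hazard ratio with 95% CI from a Cox model with the same factors. State that pathological N stage and node counts are not covariates, because the tracer can change them. State in advance how sparse strata will be merged.

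The cost is a few lines of text, and no patients or visits are added. Entry cT and cN must be carried into the analysis dataset, and with about 25-30 events some strata may need merging.

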## Discussion

3

Despite the serious burden of GC in China, the public awareness of risk factors or warning symptoms and screening is low, and there is a lack of screening programs (20). Therefore, the majority of GC are detected at an advanced stage, and at this moment, LN metastasis usually occurs. It is well known that LN metastasis is one of the most important prognostic factors for GC patients, and D2 LN dissection has gradually become the mainstream treatment to improve patient outcome (21). The mean number of LNs dissected in Western European countries was 29.5, which is slightly higher than that in China (22). This condition might be associated with the insufficient LN dissection intraoperatively and the false idea that postoperative LN dissection should be completed by a pathologist. Currently, an increasing number of studies have begun to focus on LN tracers, and an increasing number of gastrointestinal surgeons have started using carbon nanoparticle suspension injection or indocyanine green.

A number of interesting differences were identified through our analyses of CNSI and ICG. First, taking an appropriate amount of time to dissect LNs as an example, the LNs are stained black using CNSI, while the LNs labeled with ICG have the ability to generate strong fluorescence emission in certain cases. When utilizing CNSI as a tracer of LNs, surgeons can dissect the LNs under direct vision without the assistance of other instruments. However, if surgeons intend to use indocyanine fluorescence imaging to guide the postoperative nodal dissection, the fluorescence imaging mode must be available, and the wear and tear of the instrument and the burden on surgeons and operating room nurses will increase, which may prolong the time needed for dissecting the LNs. Second, compared with CNSI, ICG may have the potential to decrease the risk of anastomotic fistula with the assistance of examining the blood supply of the anastomosis. Third, CNSI extravasation into gastric serosa will contaminate the surgical fields and increase the difficulty of surgically dissecting the gastric tumor, but surgeons can switch between the fluorescence mode and normal mode to avoid the adverse effects caused by ICG extravasation (15).

There are a number of previous reviews on the effectiveness of CNSI and ICG. Chen pointed out that their team analyzed 129 GC patients in the ICG group and 129 control subjects and concluded that ICG tracer-guided LN dissection enabled the retrieval of a higher number of LNs (16). Two retrospective analyses found that fluorescence lymphography has high sensitivity and negative predictive value for the diagnosis of LN metastasis. Fluorescent lymphography-guided lymphadenectomy appears to be a reasonable alternative to conventional systematic lymphadenectomy for gastric cancer (23, 24). Similarly, in accordance with the study of Yan, carbon nanoparticles have the same efficacy and safety as a LN tracer in the clinic (11). Li et al. and our team found that CNSI is a safe material. Surgeons could harvest more LNs in patients with GC. The harvest of an increased number of smaller diameters of LNs may be beneficial. CNSI is associated with facilitating the dissection of all positive LNs, which could improve surgical quality (13, 25). However, very few studies have focused on the comparison of CNSI and ICG. A retrospective study recently conducted by our team suggested that the mean numbers of LNs and micro LNs retrieved in the CNSI group were higher than those in the ICG and control groups, and there were no differences between the ICG and control groups (15).

Whether the results of retrospective analysis can be confirmed by prospective randomized controlled clinical trials still needs to be further studied. Therefore, we are currently conducting a clinical trial to compare CNSI and ICG in detail to choose the optimal and suitable LN tracer for radical gastrectomy.

## Data availability statement

The original contributions presented in the study are included in the article/supplementary material. Further inquiries can be directed to the corresponding author.

## Ethics statement

The studies involving human participants were reviewed and approved by the Ethical Review Committee of Hebei Medical University. The patients/participants provided their written informed consent to participate in this study.
